#### Children’s Depression Rating Scale-Revised (CDRS-R)

Clinician-rated reduction of depressive symptoms, assessed by a blinded investigator after four weeks of treatment (at T2). The CDRS-R ([35, 36]) is a widely used semi-structured interview to assess clinician-rated depressive symptoms. It has been applied in various multicenter studies to assess efficiency of pharmacotherapy and psychotherapy in adolescents (e.g. TADS, [37]; ADAPT, [38]). It shows good psychometric properties (Cronbach’s Alpha = 0.85; inter-rater reliability = 0.92).

#### Antidepressant medication status

Changes in the treatment regime (initiation/cessation/dose-adjustment of antidepressants) will be assessed weekly from baseline to T2 and in the follow-ups.

#### Sleep quality and effectiveness

Change in sleep quality is assessed via the self-report Sleep-Questionnaire B (SFB/R; [39]), a well validated measure sensitive to treatment changes.

#### Level of activity

Assessed in an objective, ecological valid way via actigraphy (a watch measuring movement and light exposure before/after treatment, assessing time in bed and activity); ecological validity has been proven empirically (e.g. [40]). State-of-the-art software and algorithms will be applied to derive the parameters of interest (e.g. changes in the total degree of activity, time in bed, and sleep efficiency).

#### Health-related quality of life (HRQoL)

Changes in an individual’s perception of their wellbeing are assessed with the KIDSCREEN-10, a short, valid, and reliable self-report, providing a total score reflection of HRQoL [41].

#### Physical activity

The Child Health and Illness Profile-Adolescent Edition (CHIP-AE) is a generic measure of satisfaction with health providing several domains and subdomains. The CHIP-AE is sensitive to treatment effects in adolescents [42]. Here, the domain Resilience with the subdomain Physical Activity shall be assessed, providing information about involvement in a variety of activities related to fitness [43].

#### General psychopathology

Changes in general psychopathology are assessed via self and parent versions of the Strength and Difficulties Questionnaire (SDQ). Its change sensitivity allows estimating treatment efficacy on affective/behavioral symptoms. The validated German version [44] has, for example, been used in the KiGGS survey.

#### Alertness

BLT has direct effects on alertness. Changes in level of alertness will be assessed via the subtest “Alertness” of the Testbattery for Attentional Performance (TAP) [45].

#### Neurobiological indices of circadian function

Two “gold standard” indices of circadian function will be assessed: the DLMOand the cortisol awakening response (CAR). Changes in DLMO from before to after treatment will indicate direct impact of BLT on circadian functioning, while a low pre-treatment CAR has been reported to predict the response to BLT in adults with non-seasonal depression [46].

#### IQ

The German “Zahlen-Verbindungs-Test” (ZVT) [47] is used to assess the intelligence quotient. The ZVT is a trail-making and speed test in which participants are instructed to connect numbers from 1 to 90 which are randomly positioned on a piece of paper. It shows sufficient psychometric properties (test reliability = 0.81–0.97) [48].

#### Seasonal pattern

To control for seasonal effects, the Seasonal Pattern Assessment Questionnaire (SPAQ) will be administered to calculate a total “seasonality score” [49].

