## Background

Depressive disorders are among the most prominent health problems in youth. In adolescents, prevalence rates of depression are in the range of 5–6% [1], with a lifetime prevalence rate of 20% by late adolescence [2]. Prevalence in girls is twice as high as in boys and higher symptom load is found in youth with a high number of psychosocial risks [3]. The five-year recurrence rate in adolescent depression is as high as 40% [4]. In addition, a depressive mood during the winter season is quite common among youth in central Europe, with at least 2% of adolescents and young adults meeting criteria for seasonal affective disorder (SAD), e.g. a clinically meaningful depression with a seasonal pattern [5]. Of all depressive youth, 10% receive inpatient treatment at least once. In Germany, inpatient treatment rates for adolescent depression have increased dramatically by > 200% from 2000 to 2007, compared to 38% for all mental disorders [6].

Adolescent depression may interrupt educational attainment and thus affect human capital accumulation and future earnings. Since teenage suicide, for which depression is a principal risk factor, is the second leading cause of death in German youth, preceded only by traffic accidents [7], it is important to acknowledge that the human costs associated with depression are in a real sense greater than the economic costs. Adolescent depression is a key risk factor for adult depression; it severely impairs work and school management, leisure activities, and social contacts; frequency and degree of disabilities in depressed youth are at least as pronounced as in adults [8]. In short, depression in adolescents is prevalent, of significant public health importance, and thus a prime candidate for innovation in treatment.

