### Intervention scheme / trial flow

Inpatients from all trial sites that meet the inclusion criteria and give informed consent are consecutively included into the trial within one week after admission. After inclusion, inpatients will be interviewed by the blinded research psychologist. Initial self-report measurements and objective data in relation to depression and associated co-morbidity as well as medication are assessed by a trained diagnostician. In addition, treatment expectancy and responsibility to seasonal effects will be assessed. After the pre-treatment assessment (T1), patients are randomized to either a placebo control condition (PCC) or BLT. Both groups also receive TAU. Trial interventions will be delivered each morning (except weekends) over a period of four weeks about 7.5 h after the DLMO assessed with the MEQ.

During the intervention trial, an interim assessment with the BDI-II after two weeks will take place in order to control patient-perceived changes in depression more closely. There is no full assessment in order to reduce stress for the patients. Four weeks after completion of the treatment, individuals will again be interviewed by the blinded research psychologist and score the self-rating questionnaires as well as perform the neuropsychological assessment and deliver saliva melatonin and cortisol (post-treatment assessment; T2). Three and six months after T2, follow-up assessments will be performed via telephone and questionnaires to control for stability (T3 and T4). There is no full reassessment for neurobiological and neuropsychological data in order to facilitate the response to fulfil the follow-up assessment and to meet patients’ needs best. Moreover, AEs will be assessed in both treatment groups on a weekly basis. For an overview of the trial flow, see Fig. 1. For details on procedures per time point, see Figs. 2 and 3.

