#### Statistical analyses

The primary analysis population is the intention-to-treat (ITT) population comprising all randomized patients. Group difference in change of BDI-II rating under trial treatment will be analyzed by an analysis of covariance (ANCOVA) comprising the covariates baseline BDI-II rating, treatment group, prior pharmacological antidepressant therapy (yes/no), and sex. Missing values will be replaced by multiple imputation. The two-sided level of significance will be α = 5%. Supportive analyses are planned for the Per Protocol Population and the Completer Population. The Per Protocol Population comprises all patients from the ITT population without major protocol violations: lack of compliance with regard to therapy sessions; not meeting all inclusion criteria; meeting at least one exclusion criterion; intake of unallowed concomitant medication during the study; end of treatment visit out of schedule. In an additional sensitivity analysis, missing values will be analyzed based on the last available BDI-II rating (Last Observation Carried Forward [LOCF]). In case the LOCF approach turns out to be not conservative, an additional Baseline Observation Carried Forward (BOCF) analysis will be performed.

Further subgroup analyses are planned to detect possible differences between predictive factors (e.g. trial site, concomitant psychotropic medication for co-morbid disorders, baseline CAR and DLMO, type of depression [seasonal/non-seasonal], season, expectancy questionnaire). No interim analyses are planned. Secondary endpoints will be analyzed descriptively applying appropriate methods depending on the scale of the respective parameter. Interpretation of statistical tests must be exploratory except for the primary outcome.

AEs will be coded according to MedDRA terminology. Detailed information collected for each AE will include: a description of the event; duration; whether the AE was serious; intensity; relationship to trial treatment; action taken; and clinical outcome. Summary tables will present the number of participants observed with AEs by MedDRA System Organ Class and Preferred Term and corresponding percentages. Additional subcategories will be based on event intensity and relationship to trial treatment. A subject listing of all AEs will be prepared.

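### The SPAQ is given to control for seasonal effects, but neither its score nor the season of treatment is in the primary ANCOVA; the cost is modest precision, not bias

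*Protocol article*

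**What the plan says.** The Measurements section on seasonal pattern gives the questionnaire a purpose: "To control for seasonal effects, the Seasonal Pattern Assessment Questionnaire (SPAQ) will be administered", with a single total score as its output. The trial-flow section places this among the assessments made before randomisation: "In addition, treatment expectancy and responsibility to seasonal effects will be assessed".

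The Statistical analyses section fixes the primary model. Its terms are "baseline BDI-II rating, treatment group, prior pharmacological antidepressant therapy (yes/no), and sex". Season and depression type come later in that section, in the list of factors for further subgroup analyses: "type of depression [seasonal/non-seasonal], season, expectancy questionnaire". The same section makes the interpretation of all tests other than that of the primary outcome exploratory.

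Under Randomization and blinding procedures, the strata are prior antidepressant therapy, trial site and sex, allocated 1:1 in blocks of variable length. The trial-flow section says that patients are included consecutively.

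**The concern.** Giving a questionnaire adjusts nothing unless its score enters an analysis. The article states an aim of control and also fixes the primary model, and the two do not meet: neither the score nor the time of year is a covariate or a stratum. A subgroup analysis asks whether the treatment effect differs by season. It does not remove seasonal variation from the overall estimate.

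Season is a plausible prognostic factor on the article's own account. The Background says that "a depressive mood during the winter season is quite common among youth in central Europe", and seasonal depression is not among the listed exclusions. In a trial of light, readers will ask whether season was accounted for. At stake are the precision of the primary contrast and the handling of any seasonal imbalance that arises by chance. If such an imbalance is noticed only after unblinding, a covariate added then will look post hoc.

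**Working it through.** **Inputs from the article.** Target difference 4.37 BDI-II points, SD 10, two-sided α 5%, power 90%, 112 per arm (224 in total).

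**Assumed, because the article gives no figure.** Season and SPAQ score together explain 2% to 5% of residual BDI-II variance (R²). SD 10 is used as the residual SD, as in the article's t-test calculation.

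**1. The article's own sample size.**
- Normal approximation: n per arm = 2 × (1.960 + 1.282)² × 10² / 4.37² ≈ 110.1, rounded up to 111.
- Noncentral t: 111.01, rounded up to 112 per arm, or 224 in total. Power at 112 per arm is 90.25%.
- The stated figure is reproduced.

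**2. Gain from adjustment.** Residual SD becomes 10 × √(1 − R²), and the standard error of the difference is SD × √(2/112).

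| R² | Residual SD | Standard error | 4.37/SD | Power at 112 per arm | 224 × R² (patient equivalents) |
|---|---|---|---|---|---|
| 0 | 10.00 | 1.336 | 0.437 | 90.3% | 0 |
| 2% | 9.90 | 1.323 | 0.441 | 90.8% | 4.5 |
| 5% | 9.75 | 1.302 | 0.448 | 91.6% | 11.2 |

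**3. Bias and type I error.** These were checked by simulation: 224 patients, 4 sites × 2 × 2 = 16 strata, 4,000 runs per scenario. Further assumptions were blocks of 4 or 6, uniform entry over 2.5 years, and a sinusoidal season effect with total SD held at 10. The model was fitted without and with sine and cosine of the entry date.

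| Season amplitude (points) | Share of variance | Mean estimate, true −4.37 (without / with) | Type I error (without / with) | Power (without / with) |
|---|---|---|---|---|
| 0 | 0% | −4.36 / −4.36 | 5.2% / 5.0% | 90.1% / 90.0% |
| 2 | 2% | −4.38 / −4.37 | 4.9% / 4.9% | 90.0% / 90.2% |
| 4 | 8% | −4.35 / −4.35 | 4.7% / 4.7% | 90.2% / 92.1% |

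With 4,000 runs the Monte Carlo standard error is about 0.3 percentage points for the type I error and 0.5 for power. Leaving season out therefore shows no bias and no inflation. Including it costs nothing detectable even when season has no effect.

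**4. Chance imbalance.** In the simulation, the difference between arms in the share treated in the darker half-year had an SD of about 6.5 percentage points. Simple theory agrees: √(0.25 × 2/112) = 6.7. For a sinusoid of amplitude A, the darker and lighter halves differ on average by 4A/π points. A 2-SD imbalance (13 percentage points) would then move the unadjusted contrast as follows:
- A = 4: 0.13 × 5.09 = 0.66 points, about 15% of 4.37.
- A = 2: 0.13 × 2.55 = 0.33 points, about 8% of 4.37.

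The unadjusted standard error already allows for such shifts on average. A prespecified covariate removes the part due to season in the trial actually run.

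**The case against.** The strongest reply is that the article uses the word control loosely. The interim BDI-II and the follow-up visits are also described as means of control. The expectancy questionnaire is given to control for placebo effects and then appears only in the subgroup list, beside season. Where statistical adjustment is meant, as for antidepressant medication under Study setting and recruitment, the article says that it happens in the analyses. On this reading the Seasonal pattern section promises no covariate. That is a fair account of the usage. It does not make the subgroup analyses a form of adjustment, and the SPAQ score itself is not named anywhere in the Statistical analyses section.

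A second reply is that the gain is small and rests on an assumed R². This stands. Baseline BDI-II, already in the model, may also absorb part of any seasonal variation, so the true gain could fall below the range shown.

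Two stronger readings are tempting and are not supported:

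- **That season is left uncontrolled.** Both arms recruit over the same calendar time, in 1:1 blocks within site, so season is balanced in expectation. It is also a planned subgroup factor. It is unadjusted in the primary estimate, which is a lesser matter.
- **That stability at T3 and T4 is confounded by the change of season.** Follow-up visits three and six months after T2 do fall at another time of year. But the article nowhere says that stability will be judged by within-arm change from T2. A seasonal shift common to both arms cancels in the between-arm comparison, and follow-up modelling is commonly left to the full protocol or analysis plan.

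**Conclusion.** The point holds as a mismatch between a stated purpose and the primary model, and it is minor. The SPAQ score and season are absent from the primary ANCOVA and season is absent from the strata; the exploratory subgroup analyses do not fill that gap. The validity of the primary test is unaffected: no bias and no type I error inflation. The loss is about 0.5 to 1.4 percentage points of power (90.3% against 90.8% to 91.6%), equivalent to roughly 4 to 11 of 224 patients, plus unadjusted chance imbalance. These sizes rest on the assumed 2% to 5% of residual variance. With no seasonal effect the loss is nil; with a 4-point seasonal amplitude (8% of variance) it was about 2 points of power in the simulation.

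**What to change.** Before unblinding, add two prespecified baseline terms to the primary ANCOVA: the SPAQ seasonality score, and season at randomisation, coded for example as sine and cosine of the date or as day length. If the primary model is to stay as published, put the same terms in a prespecified sensitivity ANCOVA. Keep the subgroup analyses by season and depression type as exploratory, since they answer the separate question of effect modification. Then bring the Seasonal pattern section and the Statistical analyses section into line, so that the purpose given for the SPAQ matches its use.

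The cost is a change of analysis wording and two degrees of freedom (score plus day length) or three (score plus sine and cosine) out of 224 patients. The SPAQ is already administered before randomisation, and the date of randomisation is known for every patient. The sample size does not change.

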### Data analysis

#### Proposed sample size/power calculations

In our pilot study [20], a similar trial design was used, investigating the effects of BLT versus placebo light therapy after a treatment period of 14 days and a follow-up period of three weeks. Remission rates at the end of follow-up (week 5) were 46.7% for BLT and 25.9% for dim light. These remission rates were transformed (2*arcsin; √remission rate). The difference between the transformed remission rates resulted in Cohens h of 0.437 and was used for the calculation of the study sample. A significant difference between the two groups is defined as 3 points on the BDI-II by the NICE guidelines. A standard deviation of 10 points in the BDI-II is assumed. Thus, the proposed study aims to show a group difference of 4.37 points on the BDI-II. Calculations based on this difference yield a sample size of 224 patients (112 for each group) when using an independent t-test at a significance level of 5% and a power of 90%. Sample size was calculated using PROC POWER in SAS® Version 9.4. Drop-outs will be analyzed using multiple imputation methods.

#### Statistical analyses

The primary analysis population is the intention-to-treat (ITT) population comprising all randomized patients. Group difference in change of BDI-II rating under trial treatment will be analyzed by an analysis of covariance (ANCOVA) comprising the covariates baseline BDI-II rating, treatment group, prior pharmacological antidepressant therapy (yes/no), and sex. Missing values will be replaced by multiple imputation. The two-sided level of significance will be α = 5%. Supportive analyses are planned for the Per Protocol Population and the Completer Population. The Per Protocol Population comprises all patients from the ITT population without major protocol violations: lack of compliance with regard to therapy sessions; not meeting all inclusion criteria; meeting at least one exclusion criterion; intake of unallowed concomitant medication during the study; end of treatment visit out of schedule. In an additional sensitivity analysis, missing values will be analyzed based on the last available BDI-II rating (Last Observation Carried Forward [LOCF]). In case the LOCF approach turns out to be not conservative, an additional Baseline Observation Carried Forward (BOCF) analysis will be performed.

Further subgroup analyses are planned to detect possible differences between predictive factors (e.g. trial site, concomitant psychotropic medication for co-morbid disorders, baseline CAR and DLMO, type of depression [seasonal/non-seasonal], season, expectancy questionnaire). No interim analyses are planned. Secondary endpoints will be analyzed descriptively applying appropriate methods depending on the scale of the respective parameter. Interpretation of statistical tests must be exploratory except for the primary outcome.

AEs will be coded according to MedDRA terminology. Detailed information collected for each AE will include: a description of the event; duration; whether the AE was serious; intensity; relationship to trial treatment; action taken; and clinical outcome. Summary tables will present the number of participants observed with AEs by MedDRA System Organ Class and Preferred Term and corresponding percentages. Additional subcategories will be based on event intensity and relationship to trial treatment. A subject listing of all AEs will be prepared.

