### Study setting and recruitment

Four Departments of Child & Adolescent Psychiatry of the Universities/Medical Schools of Bochum, Ulm, Hamburg, and Brandenburg/Neuruppin participate in the study and will recruit inpatients. The study sample should reflect everyday clinical practice to be as representative as possible for inpatient youth (aged 12–18 years) with moderate to severe depression [29]. Diagnoses will be ascertained by structured clinical interviews. To maximize generalizability (i.e. testing for effectiveness), exclusion criteria are limited to situations that would prevent full participation in the study or that might require additional treatment incompatible with study treatments. Inclusion and exclusion criteria are listed in Table 1. Antidepressant medication is allowed and controlled for in the analyses performed (naturalistic approach).

**Table 1 Tab1:** Inclusion and exclusion criteria

Inclusion criteria	Moderate to severe depression (BDI-II)
	Inpatients aged 12–18 years
	Written informed consent of the inpatient and the caretaker
Exclusion criteria	Acute suicidality, bipolar 1 disorder, or schizophrenia
	Pregnancy or lactation
	Treatment with beta-blocker or with high-potency neuroleptics
	Diseases of the retina
	IQ < 70
	Non-German-speaking child or caretaker

*BDI-II* Beck Depression Inventory II

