### Randomization and blinding procedures

Potential bias is minimized by randomized treatment allocation and by blinded outcome assessment. Since patients will be blinded towards their treatment, patient-reported outcomes including the primary outcome will be blinded. Independent raters unaware of the patient’s treatment will perform further assessments (CDRS-R). Randomization is performed using the electronic case report form and will be stratified by prior pharmacological antidepressant therapy (yes/no), trial site, and sex. The randomization ratio will be 1:1 based on blocks of variable length.

Patients and clinical raters will both be blinded regarding treatment allocation. While the primary outcome (BDI-II) will be rated by the blinded patients themselves, the clinical evaluation (CGI-I, CDRS-R) will be performed by the blinded clinician. Blinding will be assured by separating diagnostic procedures from general patient and data handling. There will be one research assistant organizing recruitment and all patient-relevant data handling as well as a second person solely performing the diagnostic assessments. This procedure has proven to be feasible in our pilot study [21].

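### Trial site is a stratification factor but is missing from the primary ANCOVA, so the reported standard error is too large if site is prognostic

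*Protocol article*

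**What the plan says.** The protocol article (Randomization and blinding procedures) states that allocation "will be stratified by prior pharmacological antidepressant therapy (yes/no), trial site, and sex", and adds: "The randomization ratio will be 1:1 based on blocks of variable length". Study setting and recruitment gives the number of sites: "Four Departments of Child & Adolescent Psychiatry of the Universities/Medical Schools of Bochum, Ulm, Hamburg, and Brandenburg/Neuruppin participate in the study". With two levels each for medication and sex, that makes 4 × 2 × 2 = 16 strata.

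Statistical analyses then defines the primary model for change in BDI-II as an ANCOVA "comprising the covariates baseline BDI-II rating, treatment group, prior pharmacological antidepressant therapy (yes/no), and sex". Medication and sex are carried over from the randomisation; site is not. In the analysis, site is named only as an example for secondary exploration: "Further subgroup analyses are planned to detect possible differences between predictive factors (e.g. trial site".

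The covariate list is written as complete, while the subgroup list in the same section is openly given as examples. The point is therefore about a model the article fixes, not about a detail left to an analysis plan.

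**The concern.** Blocked randomisation within site balances the arms within each site, so differences in outcome between sites largely cancel from the treatment comparison. The standard error takes account of this only if site is in the model. Without the term, between-site variance is counted as unexplained noise although it no longer disturbs the estimate.

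Site could well be prognostic here. Both arms receive naturalistic, multimodal inpatient care, with antidepressants at the attending physician's judgment. That such care differs between four departments is an inference; the article does not say so. But the trial itself stratifies on site and lists it among possible predictive factors.

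At stake are a correctly sized test and an honest confidence interval for the primary result. The false-positive risk does not rise.

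**Working it through.** **Inputs.** Difference 4.37 BDI-II points, SD 10, two-sided 5%, power 90%, 112 patients per arm (Proposed sample size/power calculations); four sites (Study setting and recruitment). The between-site share *r* of residual variance is not given, so 0 to 20% is assumed.

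**1. The plan's own figure.** Cohen's h = 2·arcsin√0.467 − 2·arcsin√0.259 = 0.437, and 0.437 × 10 = 4.37. A two-sided 5% t-test (noncentral t) has power just under 0.900 with 111 per arm and 0.9025 with 112. The stated 224 is reproduced.

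**2. Degrees of freedom.** The model as written has five parameters (intercept, treatment, baseline, medication, sex): 224 − 5 = 219. Four sites add three parameters: 216. The critical t value is 1.971 in both cases.

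**3. Formulas.** Take a total residual SD of 10 and arms balanced within site.

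- SE reported without site: 10 × √(2/112) = 1.336
- True SE: 1.336 × √(1 − r)
- Overstatement of the SE: 1/√(1 − r) − 1
- True type I error without site: 2 × [1 − Φ(1.96/√(1 − r))]
- Power without site: Φ[(4.37 − 1.96 × 1.336)/true SE]
- Power with site: Φ[4.37/true SE − 1.96]

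For r = 10%: true SE = 1.336 × √0.90 = 1.268. Type I error = 2 × [1 − Φ(2.066)] = 0.039. Power without site = Φ(1.381) = 0.916; with site = Φ(1.487) = 0.932.

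| Assumed site share | True SE | SE too large by | Type I error, no site | Power, no site | Power, with site |
|---|---|---|---|---|---|
| 0% | 1.336 | 0% | 5.0% | 90.5% | 90.5% |
| 2% | 1.323 | 1.0% | 4.8% | 90.7% | 91.0% |
| 5% | 1.303 | 2.6% | 4.4% | 91.1% | 91.9% |
| 10% | 1.268 | 5.4% | 3.9% | 91.6% | 93.2% |
| 20% | 1.195 | 11.8% | 2.8% | 92.9% | 95.5% |

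Using t instead of normal quantiles moves these figures only slightly: at 10%, type I error is 3.8% and power 91.5% against 93.0%.

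**4. Simulation.** The design was simulated with 16 strata, permuted blocks of 4 and 6 (assumed sizes), 224 patients and 6,000 runs per setting. Mean SE and SD of the estimate are taken from the runs with a true difference of 4.37.

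| Site share | Mean SE, no site / with site | SD of the estimate, no site / with site | Type I error, no site / with site | Power, no site / with site |
|---|---|---|---|---|
| 0% | 1.34 / 1.34 | 1.31 / 1.31 | 4.6% / 4.6% | 90.6% / 90.6% |
| 5% | 1.34 / 1.31 | 1.30 / 1.29 | 4.0% / 4.5% | 91.0% / 91.7% |
| 10% | 1.34 / 1.27 | 1.28 / 1.28 | 4.3% / 5.3% | 91.0% / 92.7% |
| 20% | 1.34 / 1.20 | 1.20 / 1.19 | 2.6% / 4.4% | 92.5% / 95.3% |

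The Monte Carlo error of a simulated type I rate near 5% is √(0.05 × 0.95/6000) = 0.3 points, so single type I entries should not be over-read. The SE columns are clear. The estimate is about equally precise under both models, but only the model with site reports that precision. When site is irrelevant, the two models agree.

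**The case against.** The strongest reply is that nothing invalid happens. The estimate is unbiased, the error is conservative, and a positive result from the planned model can be trusted. The 90% power target is met in every row of the first table, and 224 was derived from an unadjusted t-test that took no credit for any covariate. In BDI-II units, the 95% half-width is 1.96 × 1.336 = 2.62 points, which is 0.07 points wider than necessary at a 5% share and 0.13 at 10%; the protocol calls 3 points relevant. All of this stands, and it limits the weight of the point.

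The power figures also assume a residual SD of 10 after adjustment, although baseline BDI-II is in the model. If the covariates explained 25% of the variance (assumption; residual SD 10 × √0.75 = 8.66), power without against with site would be 96.9% against 97.2% at a 5% share and 97.2% against 97.8% at 10%. If they explained 50%, both models would exceed 99.6% power and the gap at these shares would be at most 0.1 points. This also stands. The relative overstatement of the SE and the type I figures do not depend on the residual SD and are unaffected.

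Finally, site is not ignored, since subgroup analyses by site are planned. That does not help: such an analysis asks whether the treatment effect differs between sites and leaves the standard error of the primary comparison as it was.

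**Conclusion.** The concern holds. The primary model omits one of the three factors on which randomisation is stratified, with no stated reason. Whenever site predicts BDI-II change beyond baseline score, medication and sex, the reported standard error overstates the true one, by 2.6% at an assumed 5% site share and 5.4% at 10%. True type I error is then 4.4% or 3.9% instead of 5%. The forgone power is 0.8 or 1.5 percentage points with a residual SD of 10, and less if the baseline score explains much of the variance.

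The mismatch itself is certain; its size is not, because the site share is assumed. The loss is one of reported precision, not of validity, and the sample size stands. The change should be made because it matches the analysis to the design and costs almost nothing even if site turns out not to matter.

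**What to change.** Add trial site as a fixed effect with four levels to the primary ANCOVA, so that the model contains all three stratification factors. Include site in the multiple-imputation model too, so that imputed values preserve site differences, and use the same covariates in the Per Protocol, completer, LOCF and any BOCF analyses. The article does not describe the imputation model or the covariates of the supportive analyses; this part only keeps them consistent with the amended primary model.

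Record the change in the protocol or analysis plan before unblinding, so that the choice cannot look data-driven. The cost is one model term and 3 degrees of freedom (219 to 216). Sample size, data collection and trial conduct do not change.
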